### Plans to promote participant retention and complete follow-up {18b}

The participants will include patients with gastric cancer who need regular follow-up to monitor for cancer recurrence. We anticipate that participants will attend regular follow-ups because of concerns about cancer recurrence.

### Data management {19}

The study data will be collected and recorded electronically and stored securely on computers and hard drives at each institution. A data management system was established so that data can be accessed from the center that enters the data and the central data center. This ensured that the data were ready for accuracy checks and validation throughout the study. All data will be quality-assured, and data locking will precede the analysis.

### Confidentiality {27}

The datasets will be anonymous, and the manuscript will only include aggregate data that do not reveal the identities of the individual participants.

### Plans for collection, laboratory evaluation, and storage of biological specimens for genetic or molecular analysis in this trial/future use {33}

Not applicable, as no biological specimens were collected in this study.

## Statistical methods

### Statistical methods for primary and secondary outcomes {20a}

Intention-to-treat (ITT) analysis, which includes all patients who are randomly assigned, will be used for primary and secondary outcomes. ITT analyses provide a conservative estimate of the treatment effect and identify statistically significant differences. If consent withdrawal or dropout occurs during follow-up, the data up to the time of consent withdrawal or dropout will be used. Comparative analyses of dropout rates by arm will also be conducted. Adherence to the Wecare^®^ program will be assessed under two conditions: Wecare^®^ webpage visits and completion of the KOQUSS-40 questionnaire on the Wecare^®^ webpage. Participants who visited the webpage at least once a month during the study period and completed all questionnaires on the webpage at 1, 3, and 6 months after surgery were considered to have high adherence and were included in the per-protocol analysis. A per-protocol analysis will also be performed to evaluate the treatment effect with high compliance.

The demographic data and baseline characteristics of all randomized participants will be presented as means and standard deviations for continuous variables and as frequencies and percentages for categorical variables. A summary of the primary and secondary outcomes will also be provided, which will be compared at each time point using the chi-squared test, Fisher’s exact test, Student’s t-test (two samples), or Mann–Whitney U test, as appropriate. The primary outcome variable (QoL) will be assessed using a linear mixed model to account for the clustering of four measurements in a single patient to evaluate the effect of the Wecare^®^ intervention. For the secondary outcome variable, we present the results of between-group comparisons, considering the same clustering.

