## Interventions

### Explanation for the choice of comparators {6b}

In the intervention group, the participants were asked to use the Wecare^®^ platform (Fig. 2A~I). The Wecare^®^ platform administers QoL questionnaires, including the KOQUSS-40, following gastrectomy for gastric cancer. Based on participants’ responses, the platform automatically generates expert recommendations from gastric cancer specialists based on participants’ responses according to the timing of surgery after gastrectomy (Fig. 2C~E). Furthermore, the Wecare^®^ platform offers educational materials for gastric cancer to address the participants’ questions about the disease (Fig. 2F~I). Participants will be free to use the platform but will be asked to visit the Wecare^®^ platform at least once a month and answer questionnaires. The participants will visit an outpatient clinic before surgery and at 1, 3, and 6 months after surgery.

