**Figure 2. F2:**
[figure not shown]
Screenshots from Wecare^®^ application used by patients. **A** shows the patient’s basic information. **B** displays the diet and NRS2002 results. **C** evaluates the scores for each domain of the KOQUSS-40 questionnaire, where white indicates no to mild symptoms, blue represents intermediate symptoms, and red shows severe symptoms. **D** compares the patient’s values in each domain with the average values of a small group matched for age, gender, and operation period within an existing patient group. **E** provides automated responses regarding education and treatment for domains showing severe symptoms. **F** contains recommended educational materials from medical professionals about symptoms based on the patient’s postoperative timeline. **G** features educational materials in a card news format, primarily composed of images. **H** provides educational materials centered on text. **I** consists of educational materials presented in video format.

In the control group, participants will be asked to complete written questionnaires in the outpatient clinic before surgery and 1, 3, and 6 months after surgery. Based on the questionnaires, the clinician provides a solution at an outpatient clinic. However, the Wecare^®^ platform is not available.

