## Data collection and management

### Plans for assessment and collection of outcomes {18a}

The baseline demographic, surgical, and pathological characteristics of the patients and outcome variables were collected. Demographic and clinical characteristics were collected using an electronic case report form based on the participants’ electronic medical records. In the intervention group, questionnaire-based data will be collected using tablets at every planned visit, where the electronic questionnaire will be designed to warn the respondent about any missing values or outliers. A written questionnaire was administered to the control group. Because the data will be stored in the data center of the KOCAS ecosystem, central edit checking will be performed for all input data. A manual review of patient data will be performed in case of any error from the edit check.

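### The per-protocol set is defined by Wecare webpage use, which controls cannot have, so it yields no valid between-arm effect under high compliance

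*Protocol article*

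**What the plan says.** Section {20a} of the protocol article makes ITT, with all randomised patients, the analysis for primary and secondary outcomes. It then sets two adherence conditions, webpage visits and KOQUSS-40 completion on the webpage, and turns them into an entry rule. "Participants who visited the webpage at least once a month during the study period" and who also "completed all questionnaires on the webpage at 1, 3, and 6 months after surgery were considered to have high adherence" are the ones who "were included in the per-protocol analysis". The purpose is stated next: "A per-protocol analysis will also be performed to evaluate the treatment effect with high compliance".

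Other sections fix what each arm can do:

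- **Wecare arm, {6b}:** "Participants will be free to use the platform but will be asked to visit" at least monthly. Use is requested, not required.
- **Control arm, {6b}, text below Figure 2:** "In the control group, participants will be asked to complete written questionnaires in the outpatient clinic", and the "platform is not available" to them.
- **Control arm, {18a}:** "A written questionnaire was administered to the control group".

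No section gives controls a separate route into the per-protocol set.

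**The concern.** A per-protocol contrast needs both arms, selected in a comparable way. This rule is written wholly in terms of something that only one arm has.

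If the Wecare arm alone is filtered, its adherent members are compared with unselected controls. Adherence is voluntary and is observed after randomisation, so it may be related to recovery, motivation or ease with digital tools. The second condition adds to the imbalance. It requires the primary outcome instrument at every postoperative visit, so dropouts and incomplete responders leave the Wecare arm while equivalent controls remain.

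What is at stake is how one supplementary result is read. A difference between these two groups could come from selection alone, yet it would carry the label of a treatment effect in compliant patients.

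**Working it through.** **Set membership.** The plan states no adherence rate and no power-based figure, so there is no figure of its own to reproduce. The counts are consistent: 22 + 66 = 88, which at 1:1 gives 88/2 = 44 per arm, or 66/2 = 33 per arm in the second phase. Under the rule as written, 0 of 44 (or 0 of 33) controls qualify, so no between-arm effect can be computed. The alternative is to keep all controls and filter one arm.

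**Bias when only the Wecare arm is filtered.** Inputs, all assumed because the documents give none:

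- no true treatment effect;
- a share q of Wecare patients is adherent, namely those whose normally distributed adherence propensity exceeds the cut-off z = Φ⁻¹(1 − q);
- propensity has correlation r with QoL.

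The expected difference between arms, in SD units, is then

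bias = r × φ(z) / q

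Worked case, q = 0.6 and r = 0.3: z = −0.253, φ(z) = 0.386, bias = 0.3 × 0.386 / 0.6 = 0.193 SD.

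| Adherent share q | r = 0 | r = ±0.2 | r = ±0.3 | r = ±0.4 | r = ±0.5 |
|---|---|---|---|---|---|
| 50% | 0 | ±0.16 | ±0.24 | ±0.32 | ±0.40 |
| 60% | 0 | ±0.13 | ±0.19 | ±0.26 | ±0.32 |
| 70% | 0 | ±0.10 | ±0.15 | ±0.20 | ±0.25 |
| 80% | 0 | ±0.07 | ±0.11 | ±0.14 | ±0.18 |

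A positive sign favours Wecare (patients who feel better adhere more). A negative sign goes against it (patients with more symptoms log in more).

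**Type I error for a two-sided 0.05 t-test at one visit.** With q = 0.6 and 33 per arm, about 0.6 × 33 = 19.8 Wecare patients face 33 controls. SE = √(1/19.8 + 1/33) = 0.28 SD, and 0.193/0.284 = 0.68. The rejection probability is about P(Z > 1.96 − 0.68) + P(Z < −1.96 − 0.68) = 0.100 + 0.004 = 0.104. Simulation of 20,000 trials gave 0.104. With 44 per arm the simulated value was 0.121. At r = 0 it stayed near 0.05 throughout. Over q = 50-80% and r = 0.2-0.4, simulated values ran from 0.06 to 0.18 with 33 per arm and from 0.06 to 0.23 with 44. Because the test is two-sided, the sign of r does not change these rates.

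**The case against.** **The literal reading is strained.** The rule follows directly from a sentence about adherence to Wecare, so it may be meant for that arm only, with controls taken as given. A journal article could also leave the control rule to a fuller document. This is fair as to intent, and nobody need infer that the authors want a set without controls. But the charitable reading is the one-sided filter, so it does not rescue the stated purpose. The defect is in a rule that is printed, not in one that is absent.

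**Nothing decisive rests on this analysis.** ITT is the main analysis, the study is described as a pilot, and dropout will be compared by arm. This stands and limits the weight of the point. A reader might infer that the per-protocol result would be put forward to offset a null ITT result. The document plans no such use.

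**The direction is not known.** A reader might infer that the bias favours Wecare. The document does not support that. The platform gives guidance for severe symptoms, so sicker patients may use it more, and with r = −0.3 the same formula gives −0.19 SD. This stands.

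**The t-test is not the primary model.** Section {20a} plans a linear mixed model over four measurements, one of them preoperative. If the model estimates change from baseline, a stable QoL difference between adherers and others would partly or wholly cancel. The t-test figures fit the by-visit comparisons that {20a} also lists. They are not shown for the mixed model.

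**Selecting after randomisation is a weakness of any per-protocol set.** True, but here only one arm is selected, and that part can be avoided.

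**Conclusion.** The point holds for the per-protocol analysis only. The stated entry rule gives either no controls or a filter on the Wecare arm alone. Neither result can be read as the effect of treatment under high compliance.

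The size and direction of the bias cannot be determined from the document. With adherence of 50-80% and an absolute correlation of 0-0.5, both assumed, it lies between 0 and about 0.40 SD in either direction. If adherence is unrelated to QoL there is no bias. The example of 0.19 SD and about 10% type I error rests on 60% adherence, a correlation of 0.3, 33 per arm and a t-test at one visit.

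The ITT analysis is untouched, so the point is no ground for doubting the trial's main result. It should be corrected before analysis but is not critical.

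**What to change.** 1. Define the per-protocol set by a criterion both arms can meet: KOQUSS-40 completed at 1, 3 and 6 months, on paper or electronically.
2. Report webpage visits and webpage completion descriptively within the Wecare arm. Do not present adherent Wecare users against all controls as a treatment effect.
3. Reconcile {18a}, where the Wecare arm answers on tablets at planned visits, with {20a}, which counts webpage completion. State whether the one counts as the other, since as the rule stands this decides who is adherent.
4. Optionally add a complier-average causal effect, with randomised arm as the instrument, as a sensitivity analysis only. State its wider interval and its assumption that patients below the adherence threshold gain nothing from partial use. That assumption matters because missing one month counts as non-adherence. For illustration (assumed gains), if 60% adhere and gain 0.4 SD while the rest gain 0.2 SD, the ITT effect is 0.6 × 0.4 + 0.4 × 0.2 = 0.32 SD. The complier estimate is then 0.32/0.6 = 0.53 SD, above the true 0.4.

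The cost is a change of wording, with no new data. The common criterion removes the one-sided filter but still selects on completion after randomisation, with different response modes in the two arms. It also no longer measures compliance with the platform.

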**Methods::**

A total of 88 patients who undergo gastrectomy for gastric cancer will be randomly allocated to either the “Wecare^®^” group or the control group at a 1:1 ratio. After using the “Wecare^®^” platform for the first 22 patients and making modifications, the next 66 patients will be randomized equally. The primary outcome of this trial is the QoL among gastric cancer survivors (KOQUSS-40). The values of weight change, nutritional index change, KOQUSS-40 questionnaire compliance, self-efficacy, physical activity change, and satisfaction will be compared between the two groups as secondary outcomes. The investigator will follow-up with the patients at 1, 3, and 6 months after surgery at the outpatient clinic.

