### Outcomes {12}

The primary outcome of this trial was the QoL of the gastric cancer survivors (KOQUSS-40). The KOQUSS-40 questionnaire was developed and validated to evaluate the QoL of patients with gastric cancer who underwent gastrectomy. The questionnaire included 40 items across 11 domains, focusing on QoL related to postgastrectomy symptoms^[16]^. Using this questionnaire, we will compare each item and domain score between the groups before surgery and at 1, 3, and 6 months after surgery in the outpatient clinic.

Weight, nutritional parameters, questionnaire compliance, self-efficacy, and physical activity were compared between groups as secondary outcomes. Nutritional parameters, such as hemoglobin, albumin, and lymphocytes, and the prognostic nutritional index will be measured using common laboratory tests. Information on satisfaction with the Wecare^®^ program will also be collected.

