If the Wecare® platform demonstrates clinical efficacy, it could represent a paradigm shift in postoperative care for gastric cancer survivors. Traditionally, symptom monitoring and patient support after gastrectomy have heavily relied on face-to-face outpatient visits, which are often infrequent and reactive in nature. In contrast, Wecare® enables continuous, proactive symptom monitoring and timely feedback through a web-based system, empowering patients to engage in their own recovery process. The integration of personalized, algorithm-driven recommendations based on validated QoL data may not only improve patient outcomes – such as nutritional status, physical activity, and psychological well-being – but also reduce unnecessary clinic visits and optimize health care resource utilization. Therefore, this study has the potential to lay the groundwork for a scalable, patient-centered digital model in survivorship care after cancer surgery.

Recent studies have highlighted the expanding role of artificial intelligence and digital platforms in clinical oncology. For instance, comparative informatics analyses have demonstrated how machine learning approaches can be used to evaluate treatment strategies such as neoadjuvant versus adjuvant immunotherapy, providing new insights into personalized cancer care strategies^[20]^. Furthermore, the application of advanced AI models such as AlphaFold has accelerated progress in molecular biology and drug discovery, underscoring the transformative impact of machine learning in biomedical research^[21]^. In line with these advancements, the Wecare® platform represents a novel application of intelligent, patient-centered digital technology in the field of surgical oncology. By integrating validated QoL assessments with automated screening and personalized feedback, Wecare® has the potential to serve not only as a supportive tool for symptom management but also as a foundation for future AI-assisted clinical decision-making systems. This trial thus provides important reference value for the development of scalable, data-driven platforms that enhance long-term survivorship care in cancer patients.

In this clinical trial, we aimed to verify whether the QoL of gastric cancer patients improved by providing the Wecare^®^ platform to identify discomfort after gastrectomy and provide immediate feedback.

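### Weight, nutritional index and physical activity have no single stated contrast: the abstract compares changes, the outcomes section omits change, and the visit-wise tests leave out the pre-operative value

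*Protocol article*

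**What the plan says.** The Methods paragraph of the abstract reads: "The values of weight change, nutritional index change, KOQUSS-40 questionnaire compliance, self-efficacy, physical activity change, and satisfaction will be compared between the two groups". Three of the six items (weight, nutritional index, physical activity) are worded as changes. The other three are not.

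Outcomes {12} reads: "Weight, nutritional parameters, questionnaire compliance, self-efficacy, and physical activity were compared between groups as secondary outcomes". None of these is worded as a change. The section then splits the nutritional outcome into components: "Nutritional parameters, such as hemoglobin, albumin, and lymphocytes, and the prognostic nutritional index will be measured using common laboratory tests".

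Statistical methods {20a} describes two analyses that reach these outcomes. The first is visit by visit: "A summary of the primary and secondary outcomes will also be provided, which will be compared at each time point using the chi-squared test", followed by Fisher's exact test, Student's t-test and the Mann–Whitney test. The second comes after the linear mixed model for quality of life: "For the secondary outcome variable, we present the results of between-group comparisons, considering the same clustering". Nothing says what that second comparison contrasts, or which visit counts.

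Intervention description {11a} has the outcome variables measured before surgery and at 1, 3 and 6 months after it, so a pre-operative value is planned. Sample size {14} calls the study a pilot of feasibility and preliminary efficacy, without a power calculation.

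**The concern.** A between-group difference in the value at a visit and a between-group difference in the change up to that visit are different contrasts. With randomised groups both aim at the same treatment effect, but they have different precision and can give different answers in one data set. With about 33 or 44 patients per arm, a chance imbalance in pre-operative weight feeds straight into the first contrast and is handled differently by the second.

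Two things are at stake. The first is precision: a two-sample test at a visit sets aside a measurement that the trial has already paid for. The second is definition: while the abstract and the methods disagree, the form in which a result is reported is not settled before the data are seen. A pilot that is to feed a later main study needs stable outcome definitions, and the Discussion already names nutritional status and physical activity among the outcomes the platform might improve.

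**Working it through.** **1. The places side by side**

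| Place | Weight, nutritional index, physical activity |
|---|---|
| Abstract, Methods | change |
| Outcomes {12} | no mention of change; nutrition has four components |
| {20a}, first analysis | two-sample tests at each time point, no baseline term |
| {20a}, second analysis | clustered over visits, contrast not stated |

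I read change as change from the pre-operative value. I read the visit-wise tests as tests of the value at that visit, which is an inference: {20a} never says raw or absolute.

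**2. The article's own figure.** 11 sites × 2 patients + 11 sites × 6 patients = 22 + 66 = 88, as stated. That gives 44 per arm, or 33 per arm if only the 66 are compared. No standard deviation, effect size or correlation is given for any secondary outcome, so nothing further can be reproduced.

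**3. Precision.** Let r be the correlation between the pre-operative and follow-up values, with equal variances at both times. Relative to the standard error (SE) of the unadjusted difference in values:

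- change score: √(2(1 − r))
- adjustment for the pre-operative value: √(1 − r²)

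| r (assumed) | change / value | adjusted / value |
|---|---|---|
| 0.3 | √1.40 = 118% | √0.91 = 95% |
| 0.5 | √1.00 = 100% | √0.75 = 87% |
| 0.8 | √0.40 = 63% | √0.36 = 60% |
| 0.9 | √0.20 = 45% | √0.19 = 44% |

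The change score helps only when r exceeds 0.5 and hurts below it. Adjustment never raises the SE, apart from a negligible cost in degrees of freedom.

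**4. Cost of an open choice.** Normal data with no group effect were simulated, 40,000 trials per setting. Value and change were each tested by a two-sample t-test at two-sided 5% on the same patients. (The threshold in {20a} is printed with the inequality reversed. I read it as below 0.05; that is a separate error.)

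| r | either significant, 33 per arm | either significant, 44 per arm |
|---|---|---|
| 0.3 | 8.8% | 8.9% |
| 0.5 | 9.2% | 8.9% |
| 0.7 | 9.0% | 9.3% |
| 0.9 | 9.5% | 9.5% |

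Each test alone stayed between 4.7% and 5.2%. As a check, two unrelated tests would give 1 − 0.95² = 9.75%. The two statistics correlate at √((1 − r)/2), which is 0.59 at r = 0.3 and 0.22 at r = 0.9, so results just below 9.75% are expected.

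**5. Does the clustered comparison settle the contrast?** Not as worded. Suppose the groups are equal before surgery and differ by d at each of the three later visits. A group effect averaged over all four measurements then estimates (0 + d + d + d)/4 = 0.75d. A group-by-visit contrast at one later visit estimates d. Both account for clustering, and {20a} does not say which is meant.

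**The case against.** The strongest reply is that {20a} presents the visit-wise tests as part of a summary, and that a repeated-measures comparison follows. Since the pre-operative value is one of the four measurements, an analysis that uses baseline may already be intended. This stands in part: it is wrong to say that the plan as a whole ignores baseline. It does not remove the point, because step 5 shows that the wording leaves the contrast open, and nothing makes the clustered analysis the main one.

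Second, {20a} plans no change-score test; change appears only in the abstract. The figure of about 9% is therefore the cost of a freedom that the documents leave open, not of a procedure they prescribe. That is right, and the figure is offered only on those terms.

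Third, a reader might infer that the secondary results are open to chance findings because they carry no ranking, alpha split or exploratory label. The documents do not support that as a finding. The article is condensed, such rules are commonly left to an analysis plan that is not shown, and {14} labels the trial a pilot. The remarks on expected benefits in {11a} and in the Discussion are hedged and are not analysis claims. A family-wise rate would also need a count of tests, and the article does not say that every outcome is tested at every visit.

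Fourth, a reader might infer that the visit-wise tests lose most of their precision. That needs r of about 0.8 or more. This may be plausible for body weight, but no document supports it for laboratory values or physical activity after gastrectomy.

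**Conclusion.** The point holds for three outcomes: weight, nutritional index and physical activity. Compliance, self-efficacy and satisfaction are not worded as changes anywhere, so the contradiction does not reach them. For the three, the abstract, {12} and {20a} do not state one contrast, and the visit-wise tests omit a baseline that is available. An unseen analysis plan could add detail, but it would not remove the disagreement within the article.

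The gain from adjustment is modest at low correlation and large at high correlation: the SE falls to 95% of the unadjusted one at r = 0.3 and to 44% at r = 0.9. The range rests on assumed correlations and equal variances. The false-positive rate of about 9% applies to one outcome at one visit, and only if the choice between value and change is really made after the data are seen. Because the trial is a pilot and the primary outcome is not affected, this is a correction worth making before analysis, not a threat to the trial's main conclusion.

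**What to change.** In {20a}, define the main analysis of each continuous secondary outcome that has a pre-operative value as one baseline-adjusted between-group contrast at a named post-operative visit. The trial team chooses the visit and writes it down. Take the contrast from a repeated-measures model in one of two forms:

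- the 1, 3 and 6 month values as outcomes, with the pre-operative value as a covariate; or
- all four measurements as outcomes, with the pre-operative means constrained equal between groups.

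Use one form, not both: the pre-operative value cannot be an outcome and a covariate in the same model.

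Keep the visit-wise two-sample tests as descriptive only. Make the abstract, {12} and {20a} state the same contrast, and say which nutritional measure the abstract's index refers to. Reporting the secondary outcomes as estimates with 95% confidence intervals would suit the pilot status in {14}.

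The cost is wording in three places and a little more analysis work. No new patients, visits or measurements are needed. The one thing given up is that an isolated visit-wise p-value can no longer be presented as the result.
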